**Methods:**

This study consists of a multi-centre (two centres in Korea and two centres in China), randomised, controlled trial with three parallel arms (active acupuncture, sham acupuncture, and waitlist group). The active acupuncture and sham acupuncture groups will receive real or sham acupuncture treatment, respectively, three times per week for a total of 12 sessions over four weeks. Post-treatment follow-up will be performed a month later to complement these 12 acupuncture sessions. Participants in the waitlist group will not receive real or sham acupuncture treatments during this period but will only be required to keep recording their symptoms in a daily diary. After four weeks, the same treatment given to the active acupuncture group will be provided to the waitlist group.

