EX1 (unilateral)	Transversely, downward to the nose	20–30	Upward 1.5 cm, Rt. Lateral 1 cm to EX1

GV23 (unilateral)	Transversely, downward to the forehead with respect to the skin	20–30	Rt. Lateral 1 cm to GV23

LI4 (Both)	Perpendicular to the skin	20–30	Posterior to the web margin between the first and second phalanges

ST36 (Both)	Perpendicular to the skin	20–30	Medial 1.5 cm to ST36

In the sham acupuncture procedure, the needle will be inserted at each sham point to a depth of 3–5 mm, perpendicular to the skin, using a needle tube with a one-time rotation

Needle sites in both active and sham acupuncture groups will be swabbed with 2% boric acid before insertion. On withdrawal of the needle, dry sterilised cotton balls will be firmly applied to the insertion points. Blood pressure will be measured before and after acupuncture treatment. Before acupuncture, each participant will be evaluated by an assessor blinded to participants' random allocation, and their symptoms and total non-nasal symptom scores will be recorded. The level of any discomfort in the acupuncture or sham acupuncture will also be monitored.

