#### Outcome measures

After screening, participants who satisfied the entry requirements will begin the run-in period. During this period, participants will document the four nasal symptoms on a diary card once per day. These scores for nasal obstruction, rhinorrhea, sneezing, and itching will be summed to yield the TNSS. Each symptom is graded on a five-point scale (0 = no symptom; 1 = mild; 2 = moderate; 3 = severe; 4 = very severe). Weekly averages of TNSS will be calculated and compared among groups throughout the study period. In addition, TNSS will be reviewed by an assessor blinded to the participants' treatment group at each visit. At the end of the run-in period, the RQLQ scores will be examined in the Korean and Mandarin Chinese versions of the questionnaire [20]. RQLQ measures the influence of AR on QoL and consists of 28 items in seven domains: sleep, non-hay fever symptoms, practical problems, nose symptoms, eye symptoms, activity, and emotional function in everyday life, all based on a sum score (range: 0 – 6). The RQLQ score will be blindly assessed three times: baseline, at the end of treatment, and at the end of the follow-up period. Participants in the active acupuncture group and sham acupuncture group will record their use of PER relief medications daily during the follow-up period.

We will estimate the expectation of participants using the credibility and expectancy questionnaire to determine whether expectations affected outcomes [21]. Blinding will be assessed by asking participants what arm they thought they were in (active or sham acupuncture group, or "don't know") at the end of trial, and why they believed they were in that arm. Adverse response of acupuncture will be recorded.

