### Statistical methods

#### Analysis

Analysis will be performed for each of the following groups: 1) an intention-to-treat population consisting of all randomised participants with at least one measurable outcome report following acupuncture treatment (any missing data will be replaced with the last observation values); 2) a protocol-specific population including only participants without major protocol deviations. All data will be analysed descriptively. All main analyses will be based on the intention-to-treat population. For primary and secondary outcome measures, analysis of covariance (ANCOVA) using the differences in the change of outcome variable scores as the dependent variable, baseline outcome variable scores as the covariate, and allocated group and centres as the fixed factors will be performed. To compare the active acupuncture group with the sham acupuncture group and with the waitlist group, a single ANCOVA using dummy variables for the sham and waitlist group (thus coded 0, 0; 1, 0; 0, 1 for the active acupuncture group, sham acupuncture group, and waitlist group, respectively) will be conducted. All adverse events reported during the study will be included in the case report forms; the incidence of adverse events will be calculated. The percentage of subjects with adverse events in each group will be calculated and compared using the chi-squared test or Fisher's exact test.

Statistical analyses will be performed using the SAS statistical package program (ver. 9.1.3, SAS Institute Inc, Cary, NC), and the level of significance will be established at α = 0.05.

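### The across-group adverse-event test includes the waitlist, where capture in weeks 1–4 appears thinner than in the needled arms and where later events may follow deferred acupuncture; limit the formal test to active v sham

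*Protocol article*

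**What the plan says.** All references are to the protocol article.

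- **Test.** Analysis: "The percentage of subjects with adverse events in each group will be calculated and compared using the chi-squared test or Fisher's exact test". No pair of arms is named or left out.
- **What is counted.** Analysis: "All adverse events reported during the study will be included in the case report forms". The window is the study as a whole. Outcome measures adds: "Adverse response of acupuncture will be recorded". Data and safety monitoring lists severity and relevance to acupuncture among other information that may be collected and reported.
- **Contact in the needled arms.** Abstract, Methods: treatment is given "three times per week for a total of 12 sessions over four weeks". Under the acupuncture treatment protocol: "Before acupuncture, each participant will be evaluated by an assessor blinded to participants' random allocation", and "The level of any discomfort in the acupuncture or sham acupuncture will also be monitored".
- **Contact in the waitlist.** Abstract, Methods: over the same weeks these participants "will only be required to keep recording their symptoms in a daily diary". Outcome measures says of the diary, in describing the run-in week: "participants will document the four nasal symptoms on a diary card once per day". The same section has the RQLQ assessed at baseline, end of treatment and end of follow-up, with no arm excluded.
- **After week 4.** The Abstract (Methods) and the Exclusion criteria both say that real acupuncture is then made available to the waitlist.

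**The concern.** A comparison of adverse-event percentages is interpretable when every arm has the same opportunity to report. Active and sham have it; the waitlist, as described, does not. In the randomised weeks a needled participant meets staff 12 times, with an evaluation before needling and attention to discomfort. The text ties neither to the waitlist.

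Two things follow if the stated rule is applied to all three arms over the whole study.

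1. In weeks 1–4, a higher percentage in a needled arm than in the waitlist could reflect needling reactions, more opportunities to report, or both. The test cannot separate them, and a significant result could be read as harm from needling.
2. After week 4, events that follow deferred acupuncture would be counted under the waitlist label. This pushes the other way, so the net direction over the whole study is unclear.

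A later analysis plan could restrict the test, but it could not recover events that were not asked about in one arm.

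**Working it through.** **Step 1. Group sizes (Sample size section).** These are the only stated figures on which the test depends.

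- Adjusted SD = 4.74 × 1.148 = 5.44; difference 2.53; two-sided alpha 2.5%; power 80%. The t-test calculation gives 89.2, rounded up to 90 per arm.
- 90 × (1 − 0.76²) = 90 × 0.4224 = 38.0, the stated 38.
- Waitlist: 38/0.8 = 47.5, rounded up to 48. At 2:2:1 the needled arms have 76 each, and 76/0.8 = 95.

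The stated 95/95/48 is reproduced and not disputed. The document gives no adverse-event rate.

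**Step 2. Opportunity to report, weeks 1–4.**

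| | Active and sham | Waitlist |
|---|---|---|
| Sessions | 12 | none |
| Pre-session evaluation, discomfort monitoring | yes | not described |
| Daily diary | yes | yes |
| RQLQ and other end-of-treatment outcomes | yes | no arm excluded |
| Number of adverse-event enquiries | not stated | not stated |

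On this description capture is weaker in the waitlist. The last row is why the size cannot be derived.

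**Step 3. Illustration by contacts.** Assumptions, not document figures: the true experience is identical in both arms; each contact independently yields a report with probability q; the needled arm has 12 contacts and the waitlist k. The percentage with at least one event is 1 − (1 − q)^12 against 1 − (1 − q)^k. The last two columns give the exact probability that Fisher's test (two-sided 5%) is significant for one needled arm v waitlist, by enumerating two binomials.

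| q | k | Needled | Waitlist | 95 v 48 | 76 v 38 (after 20% withdrawal) |
|---|---|---|---|---|---|
| 2% | 1 | 21.5% | 2.0% | 95% | 86% |
| 2% | 2 | 21.5% | 4.0% | 84% | 70% |
| 2% | 4 | 21.5% | 7.8% | 53% | 41% |
| 1% | 1 | 11.4% | 1.0% | 56% | 36% |
| 1% | 2 | 11.4% | 2.0% | 41% | 27% |
| 1% | 4 | 11.4% | 3.9% | 21% | 14% |
| 0.5% | 1 | 5.8% | 0.5% | 8% | 3% |
| 0.5% | 2 | 5.8% | 1.0% | 6% | 2% |

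With equal capture (k = 12) the probability at 95 v 48 is 4.0% for q = 2% and 3.3% for q = 1%. The same holds if a single end-of-treatment enquiry recovers everything since randomisation, because the waitlist percentage is then also 1 − (1 − q)^12.

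**Step 4. A second model.** Assume a true rate of 10–40% in both arms, with the waitlist capturing only a share of what the needled arms capture. Fisher at 95 v 48 is falsely significant in:

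- 4–18% of trials at 75% capture;
- 10–64% at 50%;
- 25–98% at 25%;
- 3–4% at equal capture.

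Both models show that unequal capture alone can produce a significant result, and that its frequency depends on inputs the document does not give.

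**The case against.** The strongest reply is that the article is a condensed account. How adverse events are elicited and how the diary is laid out are commonly left to the full protocol or the case report form, and the flow chart is not shown. This stands. A reader might infer that nobody asks waitlist participants about events, or that they do nothing but fill in a nasal-symptom diary. The documents do not support either:

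- The RQLQ is assessed three times with no arm excluded.
- The non-nasal symptom score is a secondary outcome in an ANCOVA that includes the waitlist, so it must be collected there.
- The Exclusion criteria section has drugs recorded for each participant at every visit.
- The four-symptom diary is described for the run-in week and need not be its full content.

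A reader might also infer that the two statements on events contradict each other, so that the waitlist rate is zero by definition. That depends on reading the sentence about adverse responses to acupuncture alone. It can be one collection item beside the count of all events, and Data and safety monitoring already treats relevance to acupuncture as separate information.

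A third inference is that harm from going without relief medication would be missed in the waitlist. This is not established: worsening rhinitis would show in the symptom scores and the RQLQ.

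Finally, the model in Step 3 treats contacts as independent and gives a late enquiry no recall of earlier weeks, which widens the gap. That also stands, and it limits what the percentages can show.

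What survives is the rule as written: the test excludes no arm, its window runs past the start of deferred treatment, and the only contact described in detail is tied to needling.

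**Conclusion.** The concern holds in a limited form. A needled-v-waitlist test under the stated rule would mix real needling reactions with unequal ascertainment, and over the whole study it could also count needling events in the waitlist. It would be wrong to say that the comparison measures only how often people were asked, because true reactions are part of it.

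The direction of the bias in weeks 1–4 follows from the contact pattern described; its size does not. The 21–95% range at 95 v 48 rests on an assumed 1–2% per contact and an assumed one to four waitlist contacts. It falls to 6–8% at 0.5% per contact with one or two contacts, and to the nominal level or below if enquiry is equal or fully retrospective. The upper figures illustrate what unequal capture can do and are not an estimate for this trial.

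Active v sham has equal contact and is unaffected. Safety is a secondary matter here and the primary analysis is untouched, so severity is minor.

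**What to change.** In the Analysis section:

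1. Limit the formal chi-squared or Fisher test of adverse events to active v sham.
2. Report the waitlist descriptively for weeks 1–4 only, and list events after deferred acupuncture separately.
3. Count every adverse event in every arm, whether or not thought related, with relation to acupuncture as its own field. This agrees with Data and safety monitoring; word the sentence in Outcome measures to match.
4. Base any three-arm comparison only on events asked about in the same way and at the same times in all arms, for example through one adverse-event question in the daily diary.

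The cost is a few words in two sections and, if the diary route is taken, one diary line. The downside is small: no formal waitlist test for events elicited at visits, and a few more minor events to code. Sample size, randomisation and treatment do not change. The diary question has to be in place before data collection.

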## Method/design

### Objective

The aim of this study is to investigate the effectiveness of acupuncture compared with sham acupuncture or waitlist in patients with moderate to severe PER in Korea and China.

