#### Sample size

For power analysis and sample size calculation, we conducted a pilot study with a sample size of 19 (9 in the active acupuncture arm and 10 in the sham acupuncture group). In this study, the pooled SD of TNSS was 4.74 and the mean difference of TNSS change between the active and sham acupuncture group was 2.53. This difference was larger than that of recent successful acupuncture RCT on PER, reported as 1.8 [14]. TNSS reduction in the active acupuncture group in our pilot study was 4.12, higher than the minimal clinically important differences (i.e. 2.2) [22]. Therefore, the result of our pilot study showed the potential of acupuncture treatment and supported the need for the present trial. The SD of the pilot study was adjusted for better application to the true population. In order to achieve this adjustment, we multiplied the SD from the pilot data by a correction factor of 1.148. This adjustment provides a 75% probability that the resulting estimate of SD will be at least as large as the true population SD [23]. For the sample size calculation, we established a sample size (N) for an independent t test using the adjusted SD, and the difference in TNSS change between the active and sham acupuncture group with a power of 80% and alpha value of 2.5% (two-tailed). We then estimated a Pearson correlation value (R) of 0.76 between baseline and the change of TNSS in our pilot study. Finally, we multiplied N by (1-R^2^) to yield the sample size needed for ANCOVA analysis [24]. The results indicated that the number of subjects in the active acupuncture group and in the sham acupuncture group was 38. If we compare the change in TNSS for the active acupuncture group with that of the waitlist group, assuming that pooled SD and R are similar to our pilot study, the differences between groups will be larger, and thus 38 subjects in the waitlist group size will be enough to detect significant differences in the change in TNSS for the active acupuncture group. We applied a 2:2:1 ratio to the active acupuncture group, sham acupuncture group, and waitlist group, respectively, and we expect that this allocation ratio will raise the statistical power. We plan to enrol 95, 95, and 48 participants in the active acupuncture group, sham acupuncture group, and waitlisted group, respectively, allowing for a 20% withdrawal rate.

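### The active v sham comparison is sized at 2.5% two-tailed, but the analysis section sets 0.05 for two contrasts without saying whether that is overall or per contrast

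*Protocol article*

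**What the plan says.** All references are to the protocol article.

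- **Sample size.** The active v sham comparison is calculated "with a power of 80% and alpha value of 2.5% (two-tailed". The waitlist number has no calculation of its own. The figure of 38 is carried over on the argument that the difference from waitlist will be larger. No reason is given for choosing 2.5%.
- **Analysis.** "To compare the active acupuncture group with the sham acupuncture group and with the waitlist group, a single ANCOVA using dummy variables" is planned, with active acupuncture as the reference group. The section closes by naming the software and stating that "the level of significance will be established at α = 0.05". That one level covers the primary outcome, the secondary outcomes and the adverse-event comparisons.
- **Objective.** The aim is to "investigate the effectiveness of acupuncture compared with sham acupuncture or waitlist in patients with moderate to severe PER". Neither comparator is ranked above the other.
- **Primary outcome.** The variable is defined (change in weekly mean TNSS from run-in to week 4), but no contrast is named as primary.

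**The concern.** Two sections give different significance levels that bear on the same primary comparison, and nothing links them. If active v sham gives p = 0.03, the Analysis section read literally calls it positive, while the level used to size that comparison calls it negative. That choice should not be open once the data are unblinded.

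The second issue is the pair of contrasts. If each is tested at 0.05 and either may support a claim of effectiveness, the chance of at least one false positive exceeds 5%. The two contrasts also differ in evidential weight. Waitlist participants know that they are untreated and score their own symptoms in a diary, and the protocol itself expects the larger difference there. With no stated rule, that contrast could carry an effectiveness claim when the sham contrast has failed.

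**Working it through.** **Inputs (Sample size section).** Pilot SD 4.74 and difference 2.53 ("the pooled SD of TNSS was 4.74 and the mean difference of TNSS change between the active and sham acupuncture group was 2.53"); SD inflation 1.148 ("we multiplied the SD from the pilot data by a correction factor of 1.148"); R = 0.76 between baseline and change; power 80%; allocation 2:2:1; withdrawal 20%; enrolment 95/95/48. The Analysis section does not state sidedness for 0.05; two-sided is assumed.

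**Step 1. Which level produced 38?**

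- Adjusted SD = 4.74 × 1.148 = 5.44.
- ANCOVA factor = 1 − 0.76² = 0.4224.
- At 2.5% two-sided, a two-sample t test (noncentral t) needs 90 per group; 90 × 0.4224 = 38.0. The normal approximation gives 88 × 0.4224 = 37.2, which rounds up to 38.
- At 5% two-sided, the t test needs 74 per group; 74 × 0.4224 = 31.3.
- Enrolment: 38/0.8 = 47.5, so 48; 2 × 38 = 76 and 76/0.8 = 95.

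The plan's figures reproduce at 2.5% and not at 5%, so the 2.5% was really used and is not a slip of the pen.

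**Step 2. Familywise error for the primary outcome.** The contrasts share the active arm. With a common variance and 95/95/48, their correlation is

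ρ = (1/95) / √[(1/95 + 1/95)(1/95 + 1/48)] = 0.01053 / 0.02569 = 0.41.

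With both nulls true, the familywise error is 1 − P(|Z₁| ≤ c and |Z₂| ≤ c) for a bivariate normal with that correlation:

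- 0.05 each (c = 1.960): 9.3%. A simulation with a pooled-variance t gave 9.2%. Independent tests would give 1 − 0.95² = 9.75%.
- 0.025 each (c = 2.241): 4.7%. Independent tests would give 1 − 0.975² = 4.9%.

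Using 76/76/38 after withdrawals gives the same results to this precision.

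**Step 3. What the stricter level costs in power.** Residual SD = 5.44 × √0.4224 = 3.54. Approximate power = Φ(2.53/SE − c), with 76/76/38 evaluable.

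- Active v sham: SE = 3.54 × √(1/76 + 1/76) = 0.574, so 2.53/SE = 4.41. Power is 98% at 0.025 and 99% at 0.05.
- Active v waitlist: SE = 3.54 × √(1/76 + 1/38) = 0.703, so 2.53/SE = 3.60. Power is 91% at 0.025 and 95% at 0.05.

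The plan gives no numerical waitlist difference. Using 2.53 there is an assumption, in line with the plan's expectation that the waitlist difference is larger. The loss is small because the 2:2:1 ratio doubles the active and sham arms beyond the calculated 38.

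**The case against.** The best counter-argument is that the two sections can be reconciled: two contrasts at 2.5% add up to an overall 5%, and the 0.05 sits in a general closing sentence, not in a rule for the primary outcome. That reading is plausible and may well be what was intended, but the text does not state it. A literal reader would apply 0.05 to each ANCOVA coefficient.

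It can also be said that a condensed article may leave multiplicity rules to a full protocol or SAP. That is fair for the lack of a testing order, taken alone. It does not remove the disagreement between two stated levels.

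Three stronger readings are tempting, and the document does not support them:

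- **That the trial has a 9% false-positive rate.** The 9.3% needs 0.05 per contrast, success on either contrast and both nulls true. If active truly differs from waitlist, the only possible false positive is on sham, and it stays at 5% when tested at 0.05.
- **That both contrasts were sized at 2.5%.** The level is explicit only for active v sham. That it is 5% halved for two contrasts is the natural inference, not a statement in the text.
- **That the word joining the comparators in "effectiveness of acupuncture compared with sham acupuncture or waitlist" is a decision rule.** It is ordinary wording for two comparators; the Analysis section joins them with *and*. The Design section's description of a sham-controlled trial and the sham-only calculation suggest that sham is the main comparison, without saying so.

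**Conclusion.** The point stands as an inconsistency in the decision threshold for the primary outcome. The sizing level for active v sham is 2.5% two-tailed, confirmed by reproducing 38, and the analysis level is 0.05 with no indication of whether it is overall or per contrast. Results with p between 0.025 and 0.05 fall in the gap.

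The consequence for type I error is conditional. It is up to 9.3% under the three conditions named above, 4.7% at 0.025 each, and no more than 5% if 0.05 is overall or both contrasts must succeed. These figures concern the primary outcome only and assume a common variance and two-sided tests. The document does not settle which case applies, so the finding is an unresolved threshold, not a demonstrated 9% error rate. It should be settled before unblinding.

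**What to change.** Amend the Analysis section with one of two rules.

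1. **Split level, matching the sample size.** *The overall two-sided significance level for the primary outcome is 0.05. Each of the two primary contrasts, active v sham and active v waitlist, is tested at two-sided 0.025. All other tests are nominal at 5%. Success against waitlist alone will be reported as such and not as superiority over sham.* The last sentence is needed because a split level without an order still lets the waitlist contrast succeed alone.
2. **Fixed sequence at two-sided 5%.** Test active v sham first, and active v waitlist only if the first is significant. This stops the unblinded contrast from carrying the claim alone. The Sample size section should then note that sizing at 2.5% was conservative.

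**Cost.** A sentence or two, and no extra participants. Rule 1 brings a slightly stricter threshold, with the small power loss shown above. Under rule 2 no confirmatory waitlist claim is possible if the sham contrast fails.
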